## Abstract

**Background:**

Focal lesions to the articular cartilage in the knee might have demolishing consequences to the knee. There exists a wide range of possible surgical procedures targeting these injuries, however no significant differences have been found between these procedures. This may support that the improvement is a result of rehabilitation, and not the surgery itself. Arthroscopic microfracture (MF) treatment has gained popularity, and has become the treatment of choice in patients with knee cartilage defects globally. In this study we want to increase knowledge, both clinical and economic, about arthroscopic microfracture (AF) compared to arthroscopic debridement (AD) and physical rehabilitation both in the short run, and in the long run.

**Methods/Design:**

To compare arthroscopic microfracture with arthroscopic debridement and physiotherapy for the treatment of focal cartilage lesions in the knee, a long-term, double-blinded, randomized controlled multicenter trial will be conducted. A total of 114 men and non-pregnant women with a symptomatic focal full thickness cartilage lesion in the knee less than 2 cm2 will be included in the study. The two treatment allocations will receive identical rehabilitation, which is made up of 3 phases: accommodation, rehabilitation and return to activity. Follow up is 24 months, where all will be invited to participate in late follow ups after 5 and 10 years.

The Knee Injury and Osteoarthritis Outcome Score (KOOS) knee-related quality of life (QoL) subscore is the primary endpoint. Clinical parameters, questionnaires and radiologic modalities (Magnetic Resonance Imaging (MRI) and x-ray) will be used as secondary endpoints.

**Discussion:**

This is an ongoing multicenter study with a high level of evidence to compare arthroscopic microfracture with arthroscopic debridement and physiotherapy for the treatment of isolated symptomatic full thickness cartilage lesions in the knee joint.

**Trial registration:**

ClinicalTrials.gov ID: NCT02637505 (December 15, 2015).

## Background

Articular cartilage is highly specialized tissue in joints, with main functions to provide lubrication to the joint and load shearing. Since the hyaline cartilage covering the articular surface is devoid of blood vessels, lymphatic drainage and nerves, very limited intrinsic healing capacity exist [1–3]. Focal lesions to the articular cartilage in the knee might have demolishing consequences to the knee both in the short term and in the long term, due to the predisposition of early onset osteoarthritis. With a prevalence of 12 % in young adults, focal cartilage lesions are common [4]. Musculoskeletal disorders (MSDs) are the most common occupational disease in the European Union. Workers in all sectors and occupations can be affected, and this may have a major impact both socially and not least financially [5–8]. With this in mind, treatment of symptomatic articular cartilage lesions is of great interest to those who prevent and treat MSDs, as well as the patient and the society [3, 9, 10].

All types of articular cartilage repair procedures aim to repair cartilage whilst keeping options open for alternative treatments in the long term. The most common surgical interventions are arthroscopic debridement, bone marrow techniques with or without augmentation with stem cells (including microfracture and autologous matrix-induced chondrogenesis), osteochondral transplantation (autografts and allografts), cell based repairs (autologous chondrocyte implantation (ACI) and autologous mesenchymal stem cell transplant [11–13].

Arthroscopic debridement (AD) focusses on removing loose articular flaps and fibrous tissue to the subchondral bone [12]. Arthroscopic microfracture (AM) includes an AD procedure followed by drilling holes (micofractures) through the subchondral bone using an awl. This generates a blood clot (called a super-clot) which becomes fibrocartilage over time and fills the articular cartilage defect [12]. Improved knee function have been reported in some studies [14], but they have been criticized for weakness in methodology [15].

None of the various options for focal cartilage injuries have been able to demonstrate a superior outcome when compared to each other in randomized controlled trials, suggesting that the strict post-operative rehabilitation common for all techniques are more important to the clinical improvement than the cartilage surgery itself [16, 17].

Due to its minimally invasive approach, technical simplicity and low costs, microfracture treatment has gained popularity over the past decades, and has become the treatment of choice in patients with knee cartilage defects [18–23]. Microfracture is most likely not effective for larger lesions [22, 24–26], and is currently recommended for lesions below 2–4 cm^2^ [27–30]. Meta-analysis and systematic reviews have required well-designed, long-term, multicenter studies to evaluate clinical outcomes of microfracture with the use of a “no treatment” group as a control group to increase knowledge, both clinical and economic, about arthroscopic microfracture compared to arthroscopic debridement in the short and long run [10, 25, 26, 31, 32].

### Purpose

Comparing arthroscopic microfracture (AM) with arthroscopic debridement (AD) in patients with symptomatic full thickness knee cartilage defects less than 2 cm^2^ in the knee joint is the purpose of this study. The aims will be differences both in regard of subjective and objective variables at predefined times up to 24 months follow up.

## Methods and design

The study emanates from “The Norwegian Cartilage Project” (NCP). The NCP is a Norwegian project organization with a goal of improving the treatment of injured articular cartilage in the knee through five studies. The study protocol is written in collaboration with the authors behind the already published study protocol regarding ACI and debridement [33].

This multicenter study with 2 treatment arms (AM and AD) is designed as a prospective, randomized, double-blinded parallel study, see Fig. 1. The study will be conducted at Norwegian hospitals including Kristiansund Hospital, Haukeland University Hospital, Ålesund Hospital, Diakonhjemmet Hospital, Haraldsplass Deaconess Hospital, Oslo University Hospital – Ullevål and Akershus University Hospital. Each hospital will have a member of the NCP group as a local coordinator. The sponsor of the study is Akershus University Hospital, with sponsor representative professor [name].

**Fig. 1 Fig1:**
[figure not shown]
Study flow chart

Inclusion, treatment and follow-up of the patients will be done at the orthopedic clinic at each of the above mentioned hospitals. To secure double blinding at the 24 months follow up, the control will be performed by an external reviewer connected to the NCP group. Follow up is 24 months, but all will be invited to controls at 5 and 10 years respectively.

### Participants

A total of 114 non-pregnant women and men with the age between 18-50 years old will be enrolled in the study, with a cartilage defect up to 2 cm^2^ in the femoral condyles or trochlea. By using a Lysholm score less than 75 [34], we only include symptomatic defects in the study. Included patients will have normal alignment (varus or valgus less than 5° measured clinically and if uncertainty, on hip-knee-ankle (HKA) angle images), normal range of motion (ROM) (minimum 5–105°), a stable knee with no sign of radiologically osteoarthritis [35] obtained with the SynaFlex X-ray positioning frame [36]. The inclusion criteria are based on Steadman et al, Saris et al and Ulstein et al [22, 37, 38]. Prior to inclusion, written informed consent will be obtained from all subjects.

All patients will, prior to inclucion, be assessed clinically and radiologically. Using the International Cartilage Repair Society (ICRS) grading system of cartilage defects, the defect will be verified arthroscopically as a grade 3 or 4 [39]. Peroperatively arthroscopic findings such as inappropriate size of the lesion, osteoarthritis or less than 50 % normal meniscus will lead to preoperatively exclusion [40]. The operating surgeon will perform definitive inclusion of the patient in the study. According to the standard at the local hospital, excluded patients will receive appropriate treatment.

Systemic arthritis, osteoarthritis, pregnancy, language barriers, severe obesity (body mass index > 30), co-morbidities that may influence surgery or rehabilitation, alcohol, substance or drug abuse, inability to complete questionnaires or rehabilitation and psychiatric disorders are exclusion criteria, see Table 1. Previous surgery to the cartilage defects except debridement and fixation of osteochondritis dissecans lesions are also exclusion criteria. Previous alignment procedures, cruciate ligament reconstruction and meniscus surgery are not criteria for exclusion. Those who withdraw during the trials or declining enrollment will be treated according to the standard of care.

**Table 1 Tab1:** Inclusion and exclusion criteria

Inclusion criteria	Exclusion criteria
-Age 18–50 years old -Symptomatic cartilage defect -Lysholm score < 75 -Defect size less than 2 cm^2^ -Lesion graded ICRS 3–4 - > 50 % intact meniscus -Stable knee -Range of motion 5–105° -Signed written informed consent	- Systemic arthritis - Osteoarthritis - Pregnancy - Language barriers - Obesity (BMI > 30) - Comorbidities that may influence surgery or rehabilitation - Serious alcohol or drug abuse - Inability to complete questionnaires or rehabilitation - Malalignment > 5° - Earlier surgery to the chondral defect excluding OCD surgery

### Blinding and randomization

The study is designed as a double blinded study. As long as the trial lasts, the patients will not verbally nor written be informed which treatment is given to them. The operating surgeon will not be blinded, but will not be involved in the follow ups. Doctors involved in follow ups will be blinded for the given treatment. When patients are completing the questionnaires during follow ups, the case report forms (CRF) will not contain any information of the given treatment. The follow up at 24 months will be performed at each of the hospitals by an external reviewer connected to the NCP group to secure double blinding at 24 months follow up. The analysis of X-rays after 24 months will be done by an orthopaedic surgeon and a study radiologist, both blinded for the given treatment. The MRI at 24 months will be analyzed by the same blinded study radiologist.

By using a computer generator (randomization.com), the 114 participants will be randomized in blocks of six-eight (1:1) according to treatment allocations. All included participants will be given a number from 1 to 114 on inclusion. Concealed in opaque numerically marked envelopes, randomization will be printed in faded text. An employee at Kristiansund Hospital, not involved in the study, will administer the printing and concealing. The randomization will be done in the operation room during surgery, after the lesion has been graded and measured by the operating surgeon (see section “Operative procedure”).

### Arthroscopic procedure

No tourniquet is used. Three standard incisions are made. The procedure starts with a diagnostic arthroscopic examination to verify that the inclusion criteria are present. Any other necessary procedures (plica, meniscus, removal of loose bodies) are performed. Removal of lose and marginally attached cartilage is then done. Thereafter, the cartilage lesion is classified according to the ICRS classification, and measured using a standard 4-mm arthroscopic probe [39, 40]. The randomization is performed at the end of the arthroscopy (see section “Blinding and randomization) and the lesion will either undergo arthroscopic debridement (AD) or arthroscopic microfracture (AM).

#### Arthroscopic debridement

The lesion is stabilized, debriding all loose or marginally attached cartilage from the surrounding rim to form a stable edge of healthy cartilage around the defect using a ring curette, where cartilage slops down to the defect.

#### Arthroscopic microfracture

The cartilage is cut sharp forming a rim of 90°. The calcified layer is removed using a curette before an arthroscopic awl is used to perform multiple holes (“microfractures”) from the periphery towards the center. The microfractures are 3–4 mm apart and 2–4 mm deep into the subchondral bone. The correct and successful technique is confirmed by direct observation of marrow fat droplets exiting the microfracture as the fluid pump is reduced.

The instruments are removed and the incisions are sutured. Since local anesthetics may have a harmful effect on cartilage, intra-articular local anesthetics will not be used [41–43]. These surgical principles follow the techniques by Steadman and Mithoefer [24, 44–46]. Before study start, all surgeons will be given proper training in the arthroscopic study procedure.

### Post-operative protocol

Identical postoperative care will be given, usually with hospital admission up to 4 days. If there is a risk of thromboembolic disease, anti-thrombotic prophylaxis is given. Prophylactic antibiotic is not given. Up to 2 weeks of sick leave after the operation is given all participants. Any complications that should occur will be managed in a prompt manner by the involved departments.

### Rehabilitation protocol

All patients will be subjected to the same postoperative rehabilitation protocol, based on the work by Wondrasch et al [17]. The rehabilitation program will be headed by a designated study physiotherapist along with the patient’s local physiotherapist. The rehabilitation protocol involves three phases: accommodation, rehabilitation and return to activity, and is identical to the rehabilitation protocol in the previous mentioned ACI study [33], see Table 2.

**Table 2 Tab2:** Rehabilitation protocol (identical for both groups)

Rehabilitation phases	Objectives	Physiotherapy and activities	Criteria for progression to next phase
1^st^ phase: Accomodation	- Reduce symptoms^a^ - Normalize ROM og muscle control	- Education/coaching - ROM, isometric exercises - Gait training (no weight-bearing for two weeks)	- No symptoms during ADL - Flexion 90° - Normalized quadriceps
2^nd^ phase: Rehabilitation	- Full ROM - Normalize muscle strength and joint stability	- Stationary bike cycling - Progressive knee and hip resistance training - Neuromuscular training	- Full ROM - No symptoms after training - Equally distributed weight on the lower limbs during weight-bearing exercises - Ability to stand on 1 limb on a flat surface for at least 10 s
3^rd^ phase: Return to activity	- Recovery of strength and neuromuscular control - Return to activity/sport	- Knee and hip resistance training - Neuromuscular training - Cardiovascular training	- Return to activity/sport based on individual assessment

^a^ Symptoms = pain and swelling

A designated hospital physiotherapist and the surgeon will on the first postoperative day instruct the patients in range of motion exercises and gait training according to Phase 1. Within two weeks of surgery, the patient is seen by a local physiotherapist, who will supervise the rehabilitation program in liaison with the study physiotherapist.

The rehabilitation program includes both active rehabilitation and patient education, and consists primarily of knee/hip progressive resistance, neuromuscular training and cardiovascular resistance, including plyometric exercises and balance. During the physiotherapy, the patients will be explained how to perform the exercises and why they are important, adjusted to pain or other symptoms.

All patients are asked to use training diaries to provide information about the training habits. Additionally, every second week patients are asked to respond to an online survey consisting of 4 questions, all with both predefined answers (closed answers) and open answers available. The training dairy will be continued till the end of the project (24 months), while the online survey continues as long as the patients are under supervision of a physiotherapist.1^st^ phase - Accomodation:During admission in hospital, the leg is placed in a continunous passive motion (CPM) machine as tolerated, aiming to achieve 30–70° on the first postoperative day. The CPM should be used up to 6–8 h every 24 h during the hospital stay.For the first two weeks, only touch-down weight-bearing using crutches is allowed. The patients are encouraged to continue range of motion exercises, existing of 500 knee extensions/flexions three times a day, after discharge from hospital. Each patient should be scheduled to 2 to 3 supervised physical therapy sessions. When the wound is healed, swimming is allowed.Passing two weeks, weight-bearing as tolerated is carefully introduced, and gradually increased up to full weight-bearing. When the patient walks normal with limping, crutches are not needed.2^nd^ phase - Rehabilitation:The patients perform 1–2 unsupervised training sessions per week, and attend at least 2 supervised physical therapy sessions. Exercises are performed with the uninjured and injured limb. Walking with increasing distances is encouraged, and when full weight-bearing is achieved, cross-country skiing can be allowed.3^rd^ phase – Return to activity/sport:The patients perform unsupervised resistance training for a minimum of 2 and a maximum of 4 sessions per week, and attend at least 1 supervised physical therapy sessions per week. According to the goals for each patient, this phase is individualized. If return to sport is planned, sport-specific activities are included as functional progressions in the rehabilitation protocol.

### Outcome measures

Outcome measures will be the same as the endpoints in an earlier mentioned RCT coming from the same NCP group [33], enabling a direct comparison in outcome.

### Demographics

Age, gender, nationality, social status, work status, use of medication, prior medical history height in cm, weight in kg, Body Mass Index (BMI) and injury mechanism (if any) are collected at inclusion.

### Endpoints

The Knee Injury and Osteoarthritis Outcome Score (KOOS) knee-related quality of life (QoL) subscore is the primary endpoint. Validated to use in cartilage research studies, KOOS is a patient reported outcome measure [47], and will enable comparison of our results with other knee cartilage studies. At 24 months follow up, the difference in KOOS QoL subscore in the AM group compared to the AD group is the primary aim. No interim analysis is planned.

Clinical parameters, questionnaires and radiologic modalities will be used as secondary endpoints at predefined times at 3 months (±2 weeks), 6 months (±4 weeks), 12 months (±6 weeks) and 24 months (±8 weeks). They include range of motion (ROM) measured with a goniometer, visual analogue scale (VAS), all KOOS subscores except knee-related QoL, Tegner score, Lysholm score and EQ-5D. The difference between the two treatment groups and within the group will be the secondary aims. Information about work (return to work), physical activity and return to sport will also be collected.

Additionally, at the follow up after 24 months, a hop test validated by Reid [48], standing radiographs and MRI will be done. All participants will be invited to late follow ups after 5 and 10 years respectively.

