### Hypothesis

Null hypothesis: There is no difference in KOOS QoL following AM or AD treatment of a symptomatic full thickness knee cartilage defect less than 2 cm^2^ 24 months after surgery.

Alternative hypothesis: There is a difference in KOOS QoL following AM or AD treatment of a symptomatic full thickness knee cartilage defect less than 2 cm^2^ 24 months after surgery.

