### Statistical analysis

Demographic variables will be presented as mean ± standard deviation (SD) for continuous variables, and frequencies for categorical variables. The normal distribution of the variables will be tested. Given normal distribution, the statistical analysis will be performed using linear mixed models (LMM), including a random center effect for hospital. The test for the primary objective of comparing KOOS QoL from baseline to 24 months between the groups can be performed as a post hoc *t*-test following the LMM. If the data is not normally distributed, a non-parametric analysis will be done using the Mann-Whitney *U*-test. To evaluate the efficacy of treatment in terms of categorical outcome measures we plan to use Chi-squared tests. To adjust for possible confounders such as age of the patient and severity of the cartilage lesion, these variables will be included in the LMM. A *p* < 0,05 is considered statistically significant. The statistical analysis will be conducted in collaboration with a statistician at Unit for Applied Clinical Research at Norwegian University of Science and Technology, using SPSS v.22 (SPSS Inc, Chicago, Illinois) and R [49].

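### Within-group change is a secondary aim under an unrestricted p < 0.05 rule, yet a significant change within an arm cannot be attributed to microfracture or debridement

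*Protocol article*

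**What the plan says.** The Endpoints section of the protocol article sets one primary comparison, KOOS QoL between the arms at 24 months. It then lists secondary endpoints at 3, 6, 12 and 24 months: range of motion, VAS and "all KOOS subscores except knee-related QoL, Tegner score, Lysholm score and EQ-5D". For these it says: "The difference between the two treatment groups and within the group will be the secondary aims". Change within an arm is thus a declared aim, alongside the comparison of arms.

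The Statistical analysis section has a single threshold, p "< 0,05 is considered statistically significant". It does not tie this to the primary endpoint. The methods it names are a linear mixed model, a t-test after that model for the primary comparison, Mann-Whitney and chi-squared tests. None is a within-arm test.

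Three other statements bear on the point:

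- **Participants:** "By using a Lysholm score less than 75 [34], we only include symptomatic defects in the study".
- **Arthroscopic procedure:** loose and marginally attached cartilage is removed in every patient before randomisation.
- **Rehabilitation protocol:** both arms follow the same programme. The Abstract and Background themselves suggest that improvement after cartilage surgery may come from rehabilitation.

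**The concern.** A change from baseline within one arm has no control. Here it can come from at least four sources: the procedure under study, the arthroscopy and rehabilitation common to both arms, natural course, and regression to the mean. The last arises because patients are admitted on a low score, and a score selected for being low tends to be higher when measured again. Lysholm is affected directly, since it is both the entry filter and an outcome. Other scores are affected only so far as they correlate with it.

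A within-arm p-value cannot separate these sources. The trial exists to learn whether microfracture adds anything to debridement and rehabilitation, and this aim cannot inform that question. Read with an unrestricted threshold, the plan leaves room to report a significant improvement after AM, or after AD, as if it were evidence about the procedure. What is at stake is how secondary results are interpreted, not the primary conclusion.

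**Working it through.** **The plan's own figure.** The article gives no figure for within-arm change. Its sample size reproduces: a two-sample t-test for a difference of 10, SD 18, two-sided 0.05 and 80% power needs 51.84, so 52 per group, and 104 × 1.10 = 114.4, matching 114. Nothing below questions it.

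**Regression to the mean on Lysholm, with no true change**

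Inputs:

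- Cut-off 75 (Participants).
- n = 51 per arm: 114 / 2 = 57, and 57 × 0.90 = 51.3 (Sample size, 10% loss).
- Source-population mean μ = 65 to 75 and retest correlation r = 0.6 to 0.8: assumed; the article gives neither.
- σ = 18: assumed. The article states an SD of 18 only for KOOS QoL.
- Normal scores, the qualifying score serving as baseline, and a paired t-test: assumed.

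Formulas, with a = (75 − μ)/σ and λ = φ(a)/Φ(a):

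- mean of those admitted = μ − σλ
- expected spurious gain G = (1 − r)σλ
- variance of the admitted scores V = σ²(1 − aλ − λ²)
- SD of the change = √[(1 − r)²V + σ²(1 − r²)]
- non-centrality δ = G√n / SD of the change; rejection probability from the non-central t on 50 df, two-sided 0.05

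Low end (μ = 65, r = 0.8): a = 0.556 and λ = 0.3419/0.7107 = 0.481. The mean of those admitted is 65 − 8.66 = 56.34. G = 0.2 × 8.66 = 1.73. V = 162.4 and SD of change = √(0.04 × 162.4 + 324 × 0.36) = 11.10. δ = 1.73 × 7.141/11.10 = 1.11, giving a 19% rejection probability.

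High end (μ = 75, r = 0.6): a = 0 and λ = 0.798. The mean of those admitted is 75 − 14.36 = 60.64. G = 0.4 × 14.36 = 5.74. V = 117.7 and SD of change = √(0.16 × 117.7 + 324 × 0.64) = 15.04. δ = 5.74 × 7.141/15.04 = 2.73, giving 76%.

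| μ | r = 0.6 | r = 0.7 | r = 0.8 |
|---|---|---|---|
| 65 | 3.5 points, 36% | 2.6 points, 27% | 1.7 points, 19% |
| 70 | 4.5 points, 55% | 3.4 points, 43% | 2.3 points, 30% |
| 75 | 5.7 points, 76% | 4.3 points, 62% | 2.9 points, 45% |

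The nominal rate is 5%. Simulation under the same assumptions gave 1.7 to 5.8 points and 19 to 76%. Wider assumptions (mean 60 to 75, SD 15 to 18, r = 0.5 to 0.9, 52 per arm) give 0.4 to 7.2 points and about 7 to 87%.

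**A real change common to both arms.** Suppose rehabilitation or natural course moves both arms equally. Take 52 per arm, SD 18 and a baseline to follow-up correlation of 0.5, so the SD of the change is 18 × √(2 × 0.5) = 18. A shared change of 5 points is then significant in a given arm 50% of the time, 8 points 88% and 10 points 98%, although the arms do not differ.

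**The between-arm comparison.** Selection precedes randomisation, so the expected spurious gain G is the same in both arms and G − G = 0. Regression to the mean does not bias the randomised difference.

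**The case against.** The strongest reply is that the article names an aim, not a test. It specifies no paired or other within-arm test, and the mixed model could supply within-arm means with confidence intervals, which is all that is needed. The stated purpose and both hypotheses compare arms. This stands in part: the paired test above is an assumption. But the aim is stated, and the only significance rule in the article does not exclude it.

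The size also rests on assumptions. The article gives no Lysholm mean, SD or retest correlation, and does not say that the qualifying score is the baseline value. That stands. The direction of the effect under selection on a low score is firm; its magnitude is not. It acts directly on only one of the listed secondary endpoints.

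Three stronger readings are tempting and should not be drawn:

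- **That the lack of a multiplicity rule for the secondary endpoints is a defect.** Such rules are commonly left to an analysis plan, which is not shown. A count such as 9 measures × 4 visits = 36 tests is inferred, not stated, and an 84% chance of at least one false positive holds only if the tests are independent (about 45 to 73% under assumed correlations).
- **That the plan will compare arms by noting that one improved significantly and the other did not.** No such comparison appears in the article.
- **That the randomised comparisons or the primary test are compromised.** They are not.

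**Conclusion.** The point holds in a limited form. The article makes within-group change an aim, places no limit on its significance rule, and admits patients on a low value of a score that it later uses as an outcome. Because arthroscopy with removal of loose cartilage and rehabilitation are common to both arms, a significant change within an arm cannot be credited to AM or AD.

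For Lysholm, regression to the mean alone could give about 1.7 to 5.7 points and a significant within-arm result in about 19 to 76% of trials. This is conditional on normal scores, source mean 65 to 75, SD 18, retest correlation 0.6 to 0.8, 51 per arm, a paired test, and the qualifying score as baseline. These figures illustrate the problem and do not predict this trial. The qualitative conclusion does not depend on them, since the shared treatment is enough to make within-arm change uninterpretable as a procedure effect. The consequence is confined to secondary interpretation.

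**What to change.** Reword the Endpoints and Statistical analysis sections:

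1. Remove within-group change as an inferential aim. Show within-arm means or changes with 95% confidence intervals, labelled as description, without significance tests.
2. Base every secondary conclusion on the between-arm difference, adjusted for the baseline value of the same score where one is collected. Keep the planned 3, 6, 12 and 24 month visits; cutting to 24 months only would discard comparisons that the stated purpose calls for.
3. State that the p < 0.05 rule does not apply to change within an arm.

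The cost is a few sentences. Sample size, data collection and treatment stay as they are. The downside is that the report could not claim significant improvement within an arm.
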